**Methods/design:**

Forty-five subjects with pre- or stage I hypertension will be randomized into three groups: treatment group A (2 times/week), treatment group B (3 times/week), and the control group (non-treated group). The inclusion criteria will be as follows: (1) aged between 19 and 65 years; (2) prehypertension or stage I hypertension (JNC 7, Seventh Report of the Joint National Committee on the Prevention, Detection, Evaluation, and Treatment of High Blood Pressure); (3) the participants are volunteers and written consent obtained.

The participants in the treatment group A will undergo indirect moxibustion 2 times per week for 4 weeks, and the participants in the treatment group B will undergo indirect moxibustion 3 times per week for 4 weeks. The participants in the control group (non-treated group) will maintain their current lifestyle, including diet and exercise. The use of antihypertensive medication is not permitted. The primary endpoint will be a change in patient blood pressure. The secondary endpoints will be the body mass index, lipid profile, EuroQol and Heart Rate Variability. The data will be analyzed with the Student’s t-test and analysis of variance (ANOVA) (*p* < 0.05).

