### Design

This study will be a prospective randomized controlled trial, and participants will be recruited from Woo-suk University Hospital using notices at the hospital and newspaper advertisements.

In this pilot clinical trial, patients with pre- or stage I hypertension will be analyzed to determine the safety and efficacy of moxibustion, and basic analysis will be performed on the results. The study participants will voluntarily sign clinical trial consent forms, and all examinations and tests will be performed according to the clinical trial plan. Eligible subjects will be chosen based on specific inclusion and exclusion criteria. Participants will be randomized before the first treatment. Forty-five subjects with pre- or stage I hypertension will be randomized into three groups: treatment group A (2 times/week), treatment group B (3 times/week), and the control group (non-treated group). During each moxibustion treatment, each acupoint will be treated five times. The treatment will continue for 4 weeks. The follow-up assessment is designed to evaluate the long-term effects of moxibustion. Upon completion of the 4-week-long treatment, follow-up tests will be conducted at weeks 8,12,16,20 and 24 after randomization (Figure 1).

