### Randomization

This study is designed as a pilot study to calculate the appropriate sample size for future randomized clinical trials. Allowing for a 20% dropout rate, each group will include 15 participants, which is the minimum sample size necessary to evaluate the effect of moxibustion [13,14]. In this study, stratified randomization will be performed by classifying subjects into age and sex by an online centralized randomization service.

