### Outcome measures

The primary outcome measurement in this study is the change in blood pressure before randomization (baseline) and 4 weeks after randomization. Blood pressure will be taken at every visit.

The secondary outcome measures will be the mean pulse pressure, body mass index (BMI), heart rate variability (HRV), the Modified Stress Response Inventory (SRI-MF), the Pittsburgh Sleep Quality Index (PSQI), the Fatigue Severity Scale (FSS), EuroQol (EQ-5D), general assessments and blood tests including fasting blood sugar (FBS), uric acid, lipid profile, high sensitivity C-reactive protein (hs-CRP), liver function test (LFT), hemoglobin A1c (HbA1C), and complete blood count (CBC).

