### Statistical analysis

The results of the intention-to-treat (ITT) analysis will be used to assess the validity of the study as a whole. The per-protocol (PP) analysis results will be used as a reference. The ITT analysis will be used as the main safety assessment technique.

Continuous data will be represented by the average, standard deviation, minimum value, and maximum value, whereas categorical data will be represented by a frequency table. For the comparison of the results among the groups, the analysis of variance (ANOVA) test will be used when the data are normally distributed; the Kruskal-Wallis test will be used otherwise. In addition, the chi-square test will be performed for categorical data.

After 4 weeks, the differences in systolic and diastolic pressure will be summarized for each group using descriptive statistics, including the median, average, standard deviation, and interquartile range. In addition, we will evaluate the effectiveness of the treatment using an analysis of covariance as the dependent variable, the baseline score as the covariate, the group as the fixed factor, and the hypertension stage as the stratified variable. In addition, we will compare the results for the stratified groups with the results for the whole subject pool (non-stratified) to determine whether hypertension stage is a suitable stratification variable. The differences in the systolic pressure and diastolic pressure following the treatment for each group will be analyzed using a paired t-test or a Wilcoxon signed rank test, and the 95% confidence interval will be presented. To assess the difference in the tendency for each visit, repeated measures analysis of variance will be performed. A significance level of 5% will be used in all analyses.

The average pulse pressure, change in the baseline blood pressure following the treatment, BMI, EQ-5D, Ankle Brachial Pressure Index(ABI index), Brachial-Ankle Pulse wave velocity(PWV index), heart rate variation (LF/HF ratio, TP, VLF, LF, HF, heart rate, SDNN, LF norm, HF norm), and blood test results will be analyzed using the same techniques used to analyze the validity of the assessment variable. To determine whether there are differences in the distribution of the change in symptoms among the groups, analysis will be performed on each item using the chi-squared test.

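### Repeated measures ANOVA for the trend across visits by default keeps only patients with complete records, which does not fit the ITT statement or the 20% dropout allowance, and its visits are not named

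*Protocol article*

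**What the plan says.** All references are to the Protocol article.

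- **Method for the time course** (Statistical analysis): "To assess the difference in the tendency for each visit, repeated measures analysis of variance will be performed". No other analysis in that section addresses the trend over visits. Secondary variables such as pulse pressure, BMI, EQ-5D and heart rate variability are to be analysed with the same techniques.
- **Analysis set** (Statistical analysis): "The results of the intention-to-treat (ITT) analysis will be used to assess the validity of the study as a whole". The per-protocol results serve as a reference. The section gives no rule for missing values.
- **Size and dropout** (Design; Randomization): "Forty-five subjects with pre- or stage I hypertension will be randomized into three groups", and "Allowing for a 20% dropout rate, each group will include 15 participants".
- **When blood pressure is read** (Outcome measures): "Blood pressure will be taken at every visit".
- **Treatment sessions** (Abstract, Methods/design): "The participants in the treatment group A will undergo indirect moxibustion 2 times per week for 4 weeks". Group B has three sessions a week over the same period. The control group receives no treatment (Control group).
- **Assessment schedule** (Design, Follow-up and Table 2): blood pressure at baseline, at week 4, and at weeks 8, 12, 16, 20 and 24, without distinction by arm.
- **Primary comparison** (Outcome measures; Statistical analysis): change from baseline to week 4, with a separate analysis of covariance adjusted for baseline.

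**The concern.** Classical repeated measures ANOVA works on one complete set of readings per patient. Unless missing values are filled in, a patient with one absent reading leaves the whole analysis, including the visits that he or she did attend. In a trial that follows patients to week 24 and allows for 20% dropout, the method as named would therefore yield a completers analysis by default, while the same section puts ITT first.

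The second difficulty is the phrase *each visit*. Blood pressure is also read at treatment visits, and these differ in number between the arms and do not exist for the controls. The sentence does not say whether those readings enter the model or only the scheduled assessments do.

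What is at stake is the longitudinal conclusion. The Discussion promises to report how long the effect of treatment lasts, and Design and Follow-up give long-term effects as the purpose of the follow-up visits. With 15 patients per arm, losing whole records is costly in precision. If those who leave differ from those who stay, the estimated trends are also biased.

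**Working it through.** **1. The plan's own figure.** Three groups of 15 give 3 × 15 = 45. The article states no effect size, standard deviation, power or evaluable number, so 15 can only be back-calculated: 12 / (1 − 0.20) = 15. This agrees, but the 12 is inferred, so it is a consistency check and not an independent reproduction.

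**2. Complete records from dropout alone.** If all of the 20% leave before the week-24 visit and nobody else misses a visit:

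- per group: 15 × 0.80 = 12
- in total: 45 × 0.80 = 36, a loss of 9 patients

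This is the only figure that rests on the article's numbers alone.

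**3. Adding single missed visits.** There are six post-baseline time points (weeks 4, 8, 12, 16, 20, 24). The article gives no per-visit miss rate, so *m* below is an assumption, taken as independent between visits. With dropout *d*, the number of complete records is 45 × (1 − d) × (1 − m)^6.

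| Assumed m | (1 − m)^6 | d = 0 | d = 0.20 | Share of 45 at d = 0.20 |
|---|---|---|---|---|
| 0 | 1.000 | 45 | 36 | 80% |
| 2% | 0.886 | 39.9 | 31.9 | 71% |
| 5% | 0.735 | 33.1 | 26.5 | 59% |
| 10% | 0.531 | 23.9 | 19.1 | 42% |

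**4. Behaviour of the method.** One illustrative data set was simulated with 45 patients, seven time points and dropout drawn at random with probability 0.20. In it 38 patients were complete, giving 38 × 7 = 266 records out of 289 observed. A standard repeated measures ANOVA routine refused the full data as unbalanced. A mixed model with baseline among the outcomes used all 289 records from all 45 patients. If baseline is a covariate instead, as proposed below, the mixed model uses the 289 − 45 = 244 post-baseline records from the 43 patients who have any. The complete cases supply 38 × 6 = 228. This shows the mechanism; it does not forecast the size of the gain.

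**5. Which visits.** Treatment sessions are 2 × 4 = 8 in group A, 3 × 4 = 12 in group B and 0 in the control group. Suppose every session counts as a blood pressure visit, separate from baseline and week 4:

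- A: 1 + 8 + 1 + 5 = 15
- B: 1 + 12 + 1 + 5 = 19
- control: 1 + 0 + 1 + 5 = 7

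On the Table 2 schedule every arm has 1 + 1 + 5 = 7. The two readings give different data sets, and only the second has a control reading for every time point.

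**The case against.** **Missing-data rules may be elsewhere.** An article often leaves imputation to the analysis plan, which is not shown, and nothing here prescribes complete cases. The analysis might also be fitted in a form that tolerates gaps. This stands so far: the loss of incomplete patients is the default consequence of the named method, not something the article states. But the choice of method is fixed in the text, and no accompanying rule offsets the default.

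**The arms do share a schedule.** A reader might infer from the 8, 12 and 0 sessions that no common set of visits exists and that the group-by-visit comparison is undefined. The document does not support that. Design, Follow-up and Table 2 give all three arms the same seven blood pressure time points, and Table 2 is the natural reading of *each visit*. What remains is that the sentence does not tie itself to that schedule.

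**The primary result is not affected.** A reader might take the conflict with ITT to undermine the main comparison. It does not, because the week-4 change has its own analysis of covariance. The trial is also a pilot. Both facts limit the weight of the point.

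**Bias is not shown.** It is plausible that dropout depends on arm in a trial with an untreated group, but the article gives no evidence that it depends on arm or on blood pressure. The certain cost is lost data; bias is a possibility.

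**Conclusion.** The point holds, limited to the longitudinal analysis. The only method named for the trend across visits by default retains complete records only, and that does not fit the ITT statement or the dropout that the trial itself allows for. At most 36 of 45 patients would remain, provided that the full 20% leave before week 24 and that nothing is imputed. The lower figures of about 32, 26 and 19 depend on assumed, independent miss rates of 2%, 5% and 10% per visit. The visits to be analysed also need to be named.

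The week-4 comparison stands apart. What is exposed is the statement on how long the effect lasts, together with the secondary variables that are followed to week 24 and analysed in the same way. This should be changed; it is not a fault that invalidates the trial.

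**What to change.** In Statistical analysis, replace repeated measures ANOVA with a likelihood-based mixed model for repeated measures, specified as follows:

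- **Visits:** weeks 4, 8, 12, 16, 20 and 24, the post-baseline time points shared by all arms.
- **Patients:** all randomized patients with at least one reading at these visits, analysed in the group to which they were randomized. Report the number in each arm with none.
- **Terms:** group, visit, group-by-visit, baseline pressure, the randomization strata (age and sex) and, if it is kept as in the plan's analysis of covariance, hypertension stage.
- **Covariance:** unstructured, with a simpler structure prespecified in case it does not converge. Six visits mean 6 × 7 / 2 = 21 covariance parameters from at most 45 patients, so the fallback may well be needed.
- **Degrees of freedom:** Kenward-Roger.
- **Treatment-session readings:** descriptive only, because the control group has none.

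The cost is a change of wording, with standard software and no new data. The downside is small: the model assumes that data are missing at random, and the covariance structure must be fixed in advance.

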## Discussion

This study is a preliminary study targeting individuals with pre- or stage I hypertension, who will be randomly divided into treatment group A (2 times/week), treatment group B (3 times/week), and the control group (non-treated group). Basic analysis will be performed to assess the validity and safety of moxibustion for the treatment of pre- or stage I hypertension. The following results will be presented: the extent of stimulation provided by moxibustion, differences in the effect according to the frequency of treatment, and how long the efficacy of the treatment last. These results will be based on long-term follow-up observation.

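### The primary outcome does not choose systolic or diastolic pressure, and the listed between-group tests each run at 5% with none named primary, so the false-positive rate is roughly 8–16%

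*Protocol article*

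**What the plan says.** Outcome measures defines the endpoint: "The primary outcome measurement in this study is the change in blood pressure before randomization (baseline) and 4 weeks after randomization". Neither component is chosen. Statistical analysis then treats both: "the differences in systolic and diastolic pressure will be summarized for each group using descriptive statistics" after 4 weeks, and the tests that follow are also on the two pressures.

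The same section lists these tests:

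- A general rule for comparing groups: "the analysis of variance (ANOVA) test will be used when the data are normally distributed; the Kruskal-Wallis test will be used otherwise".
- An ANCOVA to evaluate effectiveness, with baseline as covariate, group as fixed factor and hypertension stage as stratification variable. The sentence does not name the dependent variable. Results with and without stage are to be compared.
- A paired t-test or Wilcoxon signed rank test within each group, for systolic and for diastolic pressure.
- A repeated measures ANOVA for the pattern over visits.

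One rule covers them all: "A significance level of 5% will be used in all analyses". There is no order among the tests. The section also lists blood pressure change again among the further outcomes. The abstract names only Student's t-test and ANOVA. The Discussion says that the results will include "differences in the effect according to the frequency of treatment".

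**The concern.** Two pressures and two between-group methods give several routes to a significant primary result, each at 5%. Nothing says in advance which one decides, so a result could be reported from whichever route is favourable. Evaluating the effect on blood pressure is the first aim under Aims of the study, so such a result would be read as evidence. The other aim, sizing a later trial, also needs one stated variable and one stated analysis.

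The group tests in ANOVA and ANCOVA are global. A significant result says that the three arms differ, but not which ones, whereas the Discussion wants to speak about treatment frequency, which is A against B.

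**Working it through.** **Inputs from the protocol article.** There are three arms: "Forty-five subjects with pre- or stage I hypertension will be randomized into three groups" (Design). On numbers, "Allowing for a 20% dropout rate, each group will include 15 participants" (Randomization), so about 15 × (1 − 0.20) = 12 complete per arm. The level is 5% per analysis, and two pressures are analysed. The article gives no overall error rate, effect size, SD or power, so there is no stated figure to reproduce.

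**Assumed, not in the document.** Systolic–diastolic correlation 0, 0.5, 0.7 or 0.8; baseline to week-4 correlation 0.6; normal data with equal variance at both times.

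**Step 1, independent tests.** The chance of at least one false positive among k independent tests at 5% is 1 − 0.95^k:

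- k = 2: 1 − 0.9025 = 9.75%
- k = 4: 1 − 0.8145 = 18.5%

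The tests here share patients and data, so they are correlated. Four tests (two pressures, two methods) must therefore give less than 18.5%.

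**Step 2, simulation without any effect.** Three arms, 12 or 15 per arm, 3,000 runs in each of the eight settings. ANOVA and Kruskal-Wallis were run on change from baseline; ANCOVA was run on the week-4 value adjusted for baseline. Hypertension stage and the repeated measures ANOVA were not simulated. The table gives the range over the eight settings of the chance that at least one test has p < 0.05.

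| Tests counted | Chance |
|---|---|
| One pressure, ANOVA | 4.5–5.3% |
| One pressure, ANOVA and ANCOVA | 6.6–7.3% |
| Both pressures, ANOVA | 7.8–10.3% |
| Both pressures, ANCOVA | 7.5–10.4% |
| Both pressures, ANOVA and ANCOVA | 10.8–14.4% |
| Both pressures, ANOVA, Kruskal-Wallis and ANCOVA | 11.7–15.7% |
| Not listed: each active arm v control, both pressures | 13.9–17.2% |
| Not listed: all three pairwise contrasts, both pressures | 18.0–23.4% |
| Listed, but within group: six paired tests | 21.7–26.5% |
| ANOVA, ANCOVA, pairwise and paired tests together | 30.3–37.4% |

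Simulation error is about √(0.05 × 0.95 / 3000) = 0.4 percentage points at 5%, and √(0.15 × 0.85 / 3000) = 0.7 at 15%.

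The listed global between-group tests on both pressures span roughly 8–16%. The upper end is generous, because Kruskal-Wallis replaces ANOVA rather than joining it. Leaving the pressure open does more than leaving the method open: about 5% rises to 8–10% for the two pressures under ANOVA, against about 7% for the two methods on one pressure.

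**Step 3, after the fix.** One pressure with one three-group test returns the rate to 5%. If both pressures stay primary, 0.05 / 2 = 0.025 each keeps the total at or below 5%.

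**Step 4, a repair that does not work.** It is natural to propose testing diastolic pressure at 5% once the systolic F-test is significant. Suppose A truly lowers systolic pressure by 2 SD, B equals control, and diastolic pressure is unaffected. The gate then opens, and two true null hypotheses (B v control on systolic, and diastolic) are each tested at 5%. Simulated false claims were about 8–10% (12–15 per arm, assumed correlation 0.5–0.7).

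**The case against.** The strongest reply is that this is a 45-person pilot with a basic analysis, that strict error control is not its purpose, and that multiplicity procedures are often left to a full protocol or SAP that is not shown. The reply also notes that the methods have different roles: only ANCOVA is tied to effectiveness, the paired tests are within arm, and the repeated measures ANOVA concerns the course over visits. Nothing says that any single p < 0.05 counts as success.

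Much of this stands. It lowers the severity, and it keeps the paired and repeated measures tests out of the 8–16%. It does not remove the point, because the primary outcome is defined in this article and left open there, and the 5% rule for every analysis is a positive statement.

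A reader might infer three stronger things that the document does not support:

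- *That the error rate is about 20%.* That size needs pairwise comparisons on both pressures, and Statistical analysis lists none between groups. Rates above 30% also need within-group results to be read as evidence of effect.
- *That the abstract contradicts the body.* ANOVA is in both, and the body's paired t-test is a Student's t-test. The abstract leaves out ANCOVA, and the body has no independent-samples t-test. This is a mismatch, partly from condensation.
- *That precision is lost through unadjusted ANOVA.* The article does not say that the ANOVA is on change scores, and the adjusted analysis is already planned.

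**Conclusion.** The point holds, at moderate severity. The article leaves the primary pressure open, tests both pressures between groups by two methods at 5% each, and labels none primary. Without a true effect, the chance of at least one significant result among the listed global tests is roughly 8–16%, for assumed systolic–diastolic correlations of 0 to 0.8 and a baseline to week-4 correlation of 0.6. It would be about 14–23% only if unlisted pairwise contrasts were added, and higher if within-group tests were taken as evidence of effect. That the rate exceeds 5% does not depend on the exact correlations within this range; its size does.

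**What to change.** - Name one primary variable, for example systolic change from baseline to week 4, and state it as the dependent variable of the ANCOVA.
- Make the baseline-adjusted three-group ANCOVA F-test at 5% the single primary analysis.
- If it is significant, test A v control, B v control and A v B, each at 5%. With three groups this is a closed procedure: if all arms are equal, the F-test holds 5%; if just two are equal, only one contrast can be falsely positive. The guarantee covers that variable only. Report the adjusted differences with 95% confidence intervals in any case.
- Label diastolic pressure secondary, without a confirmatory claim. If both pressures must stay primary, use 2.5% for each, including its pairwise contrasts.
- Label ANOVA/Kruskal-Wallis as sensitivity analyses, the paired tests as descriptive and the repeated measures ANOVA as secondary.
- Align the abstract with the body.

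This changes analysis wording only; no visit, measurement or patient procedure is affected. The cost is that a diastolic effect could not be claimed on its own, or, with both pressures primary, that each would be tested at a stricter level.

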The pulse pressure refers to the difference between the systolic pressure and the diastolic pressure. This value reflects the degree of stiffness of the blood vessels. An increase in the pulse pressure after midlife is recognized as a risk factor for cardiovascular diseases [17]. The BMI will be calculated, and laboratory tests including FBS, uric acid, lipid profile, LFT, HbA1C, and CBC will be performed before and after treatment. The subjects will fast for 12 h before blood is drawn for these tests. hs-CRP is an index used to assess the degree of risk for cardiovascular diseases and to determine prognosis [18]. After 10 min of relaxation, the HRV will be measured with electrodes attached to both wrists and ankles using QECG-3 (LXC3203, Laxtha Inc., Korea) to obtain the LF/HF ratio, TP, VLF, LF, HF, heart rate, SDNN, RMSSD, HRV index, and PNN50. The neck disability index (NDI) consists of ten questions: seven about whether the subject is able to perform functional activities, two about symptoms, and one about concentration [19]. The EQ-5D is a questionnaire that is used to assess the quality of life [20]. The subjects mark the best answers for five questions on mobility, self-care, pain, usual activities, and psychological status. The answers are given in the form of numbers (1 = no problem, 2 = moderate problem, 3 = severe problem), and the sum of the five numbers reflects the subject’s health status. Global assessments of the patients will be used to assess improvement following the treatment, as judged by the subjects [21]. The subjects can choose from five answers for questions on the degree of improvement or worsening of the blood pressure: “improved a lot,” “somewhat improved,” “no change,” “somewhat worsened,” and “worsened a lot.” The SRI-MF consists of 22 questions that are related to somatization (9 items), depression (9 items), and anger (3 items) [22]. The subjects will mark the best answer for each of the questions based on their experience in the past week. The assessment is performed by adding up the scores of each item to obtain a total score. The PSQI was used to assess the quality of sleep and to identify sleep disorders [23]. The PSQI is an index used to assess the quality of sleep and the presence of any sleep disorders in the past month. This questionnaire assesses seven items: subjective quality of sleep, latency, sleep duration, habitual sleep efficiency, factors that disturb sleep, use of sleeping aids, and impediments to daytime functioning. The FSS is a questionnaire consisting of nine items that is used to investigate the severity of fatigue during the past week [24,25]. A Pattern Identification questionnaire was developed specifically to determine whether there are differences in the distributions of the change in symptoms among the groups (Table 2).

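### The general chi-square rule for categorical data suits the five-level ordered global assessment poorly in three groups of 12 to 15; a rank or ordinal test would use the ordering and lose less power

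*Protocol article*

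**What the plan says.** All references are to the protocol article.

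- **Design** and **Randomization** set the size: "Forty-five subjects with pre- or stage I hypertension will be randomized into three groups", and "Allowing for a 20% dropout rate, each group will include 15 participants".
- **Outcome measures** describes the patient's global assessment: "The subjects can choose from five answers for questions on the degree of improvement or worsening of the blood pressure". The answers run in order from much improved, through no change, to much worse. Table 2 lists it (as general assessment) at week 4 only, with no baseline and no follow-up.
- **Statistical analysis** compares groups by ANOVA for normally distributed data, and otherwise "the Kruskal-Wallis test will be used otherwise". It then adds that "the chi-square test will be performed for categorical data". The global assessment is not in the list of secondary outcomes to be analysed in the same way as blood pressure.
- The same section says of symptom change that "analysis will be performed on each item using the chi-squared test". The wording matches the stated purpose of another instrument in Outcome measures: "A Pattern Identification questionnaire was developed specifically to determine whether there are differences in the distributions of the change in symptoms among the groups". The number and ordering of that questionnaire's answers are not stated.
- On the error rate: "A significance level of 5% will be used in all analyses".
- Fisher's exact test is named only for the incidence of abnormal reactions.

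**The concern.** The global assessment asks whether blood pressure got better or worse, so its answers carry a direction. The Pearson chi-squared test treats the five answers as unordered labels. It spreads its sensitivity over (3 - 1) x (5 - 1) = 8 degrees of freedom, where a rank test across three groups uses 2. It also relies on a large-sample approximation in a table with few participants per cell.

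At stake is the chance of detecting a real shift towards improvement in this secondary outcome. Because the sparse cells make the test conservative, the cost is missed effects and not false positives.

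**Working it through.** **1. Participants per group.** 45 / 3 = 15 randomized. With 20% dropout, 15 x 0.8 = 12 remain. This agrees with the plan's own figure, since 12 / 0.8 = 15. The article states no power, category probabilities or effect size, so there is no planned power to reproduce.

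**2. Average expected count in a 3 x 5 table.** 36 / 15 = 2.4 and 45 / 15 = 3.0.

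**3. Minimum share of sparse cells.** With equal groups, a cell's expected count is its column total divided by 3, so it reaches 5 only if the column total is at least 15.
- At 45 participants, three columns of 15 would use everyone and leave two answers empty. If all five answers are used, at most two columns can reach 15.
- At 36 participants, two columns of 15 leave 6, so again at most two can reach it.
- Hence at least 3 of 5 columns, or 9 of 15 cells (60%), are below 5, whatever the distribution. If only four answers are used, at least half are.

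**4. A worked example (assumed inputs).** Take a control distribution of 5/25/45/20/5% from best to worst answer, and a common odds ratio of 5 for a better answer in both treated groups. The control cumulative proportions are 0.05, 0.30, 0.75 and 0.95. Multiplying each odds by 5 gives 0.208, 0.682, 0.938 and 0.990, so the treated distribution is about 21/47/26/5/1%. Simulated rejection rates at 5%, Pearson chi-squared (empty columns dropped) against tie-corrected Kruskal-Wallis:

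| Assumed odds ratio | 12 per group: chi-squared / Kruskal-Wallis | 15 per group: chi-squared / Kruskal-Wallis |
|---|---|---|
| 3 | 12% / 27% | 15% / 34% |
| 5 | 26% / 53% | 35% / 65% |

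With no difference between groups, the size was 3.0 to 3.3% for chi-squared and 4.6 to 4.7% for Kruskal-Wallis. About 84% of expected counts (12 per group) and 77% (15 per group) were below 5. A repeat with 40,000 simulated trials per setting agreed to within about one percentage point.

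**5. A wider range (assumed inputs).** Four control distributions (uniform, symmetric and two peaked at no change) were crossed with odds ratios for control/A/B of 1/2/4, 1/3/6, 1/4/4, 1/6/6 and 1/3/10, with 40,000 trials each:

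| | 12 per group | 15 per group |
|---|---|---|
| Chi-squared power | 12 to 45% | 17 to 59% |
| Kruskal-Wallis power | 29 to 75% | 36 to 85% |
| Ratio | 0.43 to 0.62 | 0.46 to 0.70 |

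Size was 2.5 to 4.6% for chi-squared and 4.5 to 4.8% for Kruskal-Wallis.

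**6. Large-sample check.** At equal noncentrality, 2-df power of 50%, 80% and 90% corresponds to 8-df power of 29%, 57% and 71%. The direction agrees, and part of the loss is due to degrees of freedom alone.

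**7. Where the loss shrinks or reverses.**
- Three ordered levels: the ratio is 0.70 to 0.84.
- Yes/no items: no loss (1.03 to 1.07).
- A difference in spread with no shift (assumed control 10/20/40/20/10%, A 30/15/10/15/30%, B 40/5/10/5/40%): chi-squared 57% against Kruskal-Wallis 6% at 12 per group.

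**The case against.** **The test for the global assessment is inferred.** Statistical analysis never names this outcome, and one could argue that the Kruskal-Wallis clause for non-normal data reaches it. That stands as a caveat. Still, a choice among five verbal answers is more naturally categorical data. With no baseline, the covariance, paired and repeated-measures analyses cannot apply to it. If Kruskal-Wallis was intended, one sentence would settle it.

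**A reader might infer that the item-by-item sentence itself concerns five ordered answers.** The article does not support that. The sentence points to the Pattern Identification items, whose scale is not given; if those are yes/no, no power is lost. The point on those items is therefore conditional.

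**A reader might infer that power is halved in general.** That depends on assumed distributions and on a location shift. It fits small to moderate shifts on five levels, but at the largest effects chi-squared kept 60 to 70%.

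**A reader might infer that the p-values cannot be trusted.** Simulated size stayed below 5% in every five-level setting, so the test is conservative there and not misleading in the direction of false claims.

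**The plan asks about distributions, so an omnibus test is defensible.** For symptom change this has force, and a rank test does have little power for a pure spread difference. For the global assessment, whose answers grade improvement against worsening, a shift is the question of interest.

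**This is a pilot and the outcome is secondary.** That is right, and it limits the weight of the point. Even the better test has only 27 to 34% power at an odds ratio of 3.

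**Conclusion.** The point holds as a minor improvement. For the five-level global assessment, the stated categorical rule leads to a test with at least 60% of cells below an expected count of 5 when all answers are used. The test is conservative and discards the ordering. Under the assumed shifts it gives up about 30 to 57% of the power of a rank test already named in the plan.

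The sparse-cell result rests only on the plan's group sizes and equal groups. The power figures rest on assumed category probabilities and odds ratios, and on a shift in location. For the Pattern Identification items the conclusion applies only where the answers are ordered. The blood pressure analysis is not affected.

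**What to change.** Replace the general chi-square sentence, for these outcomes, with wording such as: *The patient global assessment, and each Pattern Identification item with ordered answers, will be compared among groups by the Kruskal-Wallis test or by a proportional-odds model with group as factor, and pairwise differences will be reported with 95% confidence intervals. Binary or unordered items with small expected counts will be compared by the Fisher-Freeman-Halton exact test.* Also state the answer scale of the Pattern Identification items, so that it is clear which test applies to each.

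The cost is a sentence or two and no new data. The one trade-off is weak power for a difference in spread without a shift. Tabulating the full distribution of answers by group would leave such a pattern visible.
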